#### 11.5.2.4 SAFETY ANALYSES

Safety data will be summarized for the safety population.

#### 11.5.2.5 KEY SAFETY ENDPOINTS

Rate of early (symptomatic, and asymptomatic) intracranial haemorrhages detected with neuroimaging, incidence of major extracranial haemorrhages, deaths, recurrent ischaemic strokes, neurological deteriorations will be analysed in the same way as secondary endpoints.

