r – Assessments in brackets are optional (to allow data collection if available), and if they interfere with standard diagnostic assessments, they are not clinically justified, or may significantly delay initiation of investigational treatment may not be performed; missing data for these assessments will be not considered as protocol deviations.

s - The test should be performed at least once during hospitalization (V0-V3)

t - Obligatory only in cases where the screening value was beyond that defined in inclusion/exclusion criteria.

u - ECG must be performed preferably within the first 24 hours from AIS but not later than 72 hours.

w- Review of safety endpoints: any symptomatic intracranial haemorrhage (sICH), any life threatening extracranial bleeding, recurrent or new acute thromboembolic stroke, any life threatening thromboembolic complications, any significant allergic reactions assumed to be related with the administered substances (antidotes, rtPA).

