### 2.3.1 KNOWN POTENTIAL RISKS

Patients with AIS are the population with multiple and various comorbidities, and high total cardiovascular risk.

The most severe complication related to rtPA administration is symptomatic intracerebral haemorrhage (sICH), which occurs in 3-7% of all treated patients, and is associated with poor functional outcome (Hacke W et al, 2008) (Sandercock P et al, 2012) (Karaszewski B et al, 2015) (Yaghi S et al., 2014). Meta-analysis of nine trials of rtPA in ischemic stroke (Whiteley WN et al, 2016) showed increased risk of type 2 parenchymal haemorrhage (PH2), of haemorrhage as per SITS-MOST definition, and fatal intracerebral haemorrhage in IVT group.

In REVERSE-AD trial (A Study of the RE-VERSAl Effects of Idarucizumab on Active Dabigatran), a multicentre, prospective, open-label study, patients with life-threatening or uncontrolled bleeding and patients who required emergency surgery or other urgent procedures, were treated with 5.0 g of intravenous idarucizumab. Median maximum reversal value was 100% in the first 4 hrs. Most patients achieved complete reversal as measured by ECT (82%), or dTT (99%). The adverse reactions reported in ≥5% of patients were constipation and nausea. In 33 (6.56%) patients reported thrombotic

events, and most of these patients were not on antithrombotic therapy at the time of the event (Pollack CV et al, 2017).

In ANNEXA-4 trial (The Andexanet Alfa, a Novel Antidote to the Anticoagulation Effects of Factor Xa Inhibitors), a single-group cohort study, patients with acute major bleeding – 64% intracranial and 26% gastrointestinal – were treated with andexanet alfa in intravenous bolus over 30 minutes, followed by continuous infusion for 120 min. Median anti-FXa activity decreased was 92% for both apixaban and rivaroxaban patients. There were 34 patients (10%) with a thrombotic event during 30-day follow-up period (Connolly SJ et al, 2019).

---

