### 2.3.2 KNOWN POTENTIAL BENEFITS

Specific AIS treatment therapies – intravenous thrombolysis (IVT) and mechanical thrombectomy (MT), combined with comprehensive, interdisciplinary care provided by stroke units significantly improve chances for excellent and good functional outcomes (mRS 0-1 and 0-2, respectively).

Reversing NOAC activity with administration of fast-acting specific reversal agents (antidotes): idarucizumab for dabigatran, and andexanet alfa for apixaban or rivaroxaban, has been shown to be an effective and safe emergency treatment for major, life-threatening bleeding complications of NOAC therapy, or as a prevention of bleeding in patients requiring emergency surgery, or invasive procedures (Ondexxya SmPC, 2020) (Praxbind SmPC, 2020).

Taking that maximum reversal effect of idarucizumab is observed within few minutes from bolus administration, and high proportion of patients show complete neutralization of anticoagulant activity (Ondexxya SmPC, 2020) (Praxbind SmPC, 2020). it is possible that the sequential reperfusion intravenous therapy with rtPA soon after idarucizumab might result in outcomes similar to those observed in large rtPA stroke trials.

Similar benefits might be expected from reversing anti-Xa activities by andexanet alfa followed by administration of intravenous rtPA. However, there is no single empiric data of this therapeutic approach, and the mechanisms of action with all pharmacodynamic and pharmacokinetic characteristics, and potential harms related to not only bleeding, but also thromboembolic complications as assumed from complex pathophysiological relations, are different for andexanet alfa in comparison to idarucizumab.

---

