| To assess characteristics of major clinically significant extracranial bleedings after the investigational therapy in patients with acute ischaemic stroke on the non-vitamin K antagonist oral anticoagulants compared to placebo. | Incidence and severity of major extracranial haemorrhages defined as:
- fatal
- severe enough to require transfusion or surgery
- an absolute decrease in haemoglobin $> 5$ g/dL
- a decrease in haematocrit of $> 15\%$
- bleeding in persistent or temporary serious disability)                                                                                                                                                                                                                                                                  |
| To assess overall safety profile of the investigational therapy in patients with acute ischaemic stroke on the non-vitamin K antagonist oral anticoagulants compared to placebo.                                                    | Incidence and category of AEs reported during the study.                                                                                                                                                                                                                                                                                                                                                                                                                                                                                                           |

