### 9.2.1 EVENTS OF SPECIAL INTEREST

Events of Special Interest (ESI) are those events thought to be associated, or potentially associated with the investigational treatment and/or AIS course. In the STROACT study there are prespecified AEs / events which are considered as ESI. These events will be monitored during the study and will be analysed as the critical safety endpoints comparing the study treatment and placebo groups.

1. Mortality recorded on the day of visit 3, 4, 5 (equal to 7-, 30- and 90 days after AIS)
2. Cerebrovascular events at 7-, 30- and 90-days post AIS:
  - Recurrent ischaemic stroke
  - Neurological deterioration (NIHSS).
3. Incidence of intracranial bleeding (symptomatic and asymptomatic) assessed with CT/MRI and assessed according to European Cooperative Acute Stroke Study (ECASS II) classification at 24h +/- 4 hours and 7 days +/- 1 day after study treatment administration (please see [Section 9.1.3.3](#)).
4. Incidence and severity of major extracranial haemorrhage defined as:
  - fatal
  - severe enough to require transfusion or operation
  - an absolute decrease in haemoglobin >5 g/dL
  - a decrease in haematocrit of >15%
  - bleeding associated with persistent or serious disability).
5. Post-treatment thromboembolic and cardiovascular events.

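### Section 9.2.1 promises a comparison of all thromboembolic and cardiovascular events, but sections 3.2 and 11.5.2.5 carry only recurrent ischaemic stroke, and the visit review narrows the rest to life-threatening events

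*Protocol*

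**What the plan says.** Section 9.2.1 lists five events of special interest. The fifth is "Post-treatment thromboembolic and cardiovascular events", with no severity limit, components or time point. The section says that such events "will be analysed as the critical safety endpoints comparing the study treatment and placebo groups". Section 14.1.3 repeats both statements.

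Section 3.2 (and the synopsis, 1.1.3.2) sets the secondary safety endpoints: deaths; non-fatal recurrent ischaemic stroke, haemorrhagic stroke and neurological deterioration; intracranial haemorrhage on imaging; major extracranial haemorrhage; and adverse events overall. Section 11.5.2.5 then names the key safety endpoints for analysis: "Rate of early (symptomatic, and asymptomatic) intracranial haemorrhages detected with neuroimaging, incidence of major extracranial haemorrhages, deaths, recurrent ischaemic strokes, neurological deteriorations". Neither place has a general thromboembolic or cardiovascular item.

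The visit safety-endpoint review (section 1.3 note w, repeated in 6.5.2 to 6.5.6) asks about new or recurrent thromboembolic stroke without a severity limit. It also asks about "any life threatening thromboembolic complications" and "any life threatening extracranial bleeding". Section 9.2 refers to the visit descriptions for the definition of safety points.

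The protocol names the risk itself. Section 2.3.1 cites 33 patients (6.56%) with thrombotic events in the idarucizumab study and, for andexanet alfa, "There were 34 patients (10%) with a thrombotic event during 30-day follow-up period". Section 2.3.2 speaks of "potential harms related to not only bleeding, but also thromboembolic complications".

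**The concern.** The study treatment reverses anticoagulation in patients who were taking it to prevent clots. Thrombosis is therefore one of the harms a reader of the report will look for first. The protocol defines that outcome in three ways: all such events (9.2.1, 14.1.3), recurrent ischaemic stroke alone (3.2, 11.5.2.5), and stroke plus whatever else is life threatening (visit review). Which definition is used decides whether a deep vein thrombosis, a non-massive pulmonary embolism, a myocardial infarction or a limb embolus counts in the between-group safety comparison.

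The bleeding item has the same mismatch. Section 3.2 counts an extracranial bleed as major if, among other criteria, it is "severe enough to require transfusion or surgery". The visit review asks only about life-threatening bleeds, so a bleed can meet the protocol's definition of major and still fall outside the question put at the visit.

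**Working it through.** **1. The passages side by side**

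| Place | Thromboembolism | Extracranial bleeding |
|---|---|---|
| 9.2.1, 14.1.3 | All thromboembolic and cardiovascular events; compared with placebo | Major, by listed criteria |
| 3.2 | Recurrent ischaemic stroke only | Major, by listed criteria |
| 11.5.2.5 | Recurrent ischaemic stroke only | Major |
| Note w, 6.5.2–6.5.6 | Thromboembolic stroke without limit; other events only if life threatening | Only if life threatening |
| 9.3.2, 11.5.2.6 | Any adverse event recorded; treatment-emergent events tabulated by SOC and preferred term | Same |

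**2. Two events followed through the text**

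- *A deep vein thrombosis on Day 12, not life threatening.* It is a critical safety endpoint under 9.2.1. It is not a secondary endpoint under 3.2, is not analysed under 11.5.2.5, and gives a negative answer in the visit review. It is recorded as an adverse event and appears under its own preferred term. None of the overview categories compared in 11.5.2.6 groups thromboembolic events.
- *An extracranial bleed needing transfusion but judged not life threatening.* It is major under 3.2 and 9.2.1 and belongs in the 11.5.2.5 analysis, but gives a negative answer in the visit review. It is in the adverse event data. If the endpoint count is built from the visit-review item, it is missed.

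The narrower list also reaches oversight. Section 10.3.3 has the IDMC review safety endpoints, and the early safety analysis (11.5.4.2) covers safety endpoints. Serious adverse events and adverse event listings respectively are supplied as well, which limits the loss.

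**3. Expected size**

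Inputs: 46 patients per treatment group within each arm (11.3); thrombotic rates of 6.56% and 10% (2.3.1).

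The plan's 46 is reproduced closely. With 40% in both groups, a 15-point margin, one-sided 0.2 and 70% power:

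n = 2 × 0.40 × 0.60 × (0.842 + 0.524)² / 0.15² = 39.8, so 40.

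Allowing 10% drop-out, 40 / 0.9 = 44.4, so 45. One interim look (spending parameter of −4 assumed) inflates this by about 1.006 and leaves it at 45. The stated 46 is accepted.

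Expected active-group patients with a thrombotic event, per arm:

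- dabigatran arm: 46 × 0.0656 = 3.0
- apixaban or rivaroxaban arm: 46 × 0.10 = 4.6

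**4. What a comparison could show**

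The protocol gives no placebo rate; 2% to 5% is assumed here. Approximate power per arm (two-sided 0.05, n = 46 per group) is

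Φ{(|p₁ − p₀| − 1.96·√[2p̄(1 − p̄)/n]) / √[p₁(1 − p₁)/n + p₀(1 − p₀)/n]}.

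- Active 6.56% against placebo 2%: (0.0456 − 1.96 × 0.0422)/0.0419 = −0.89, power about 19%. Against 5%, power is about 5%.
- Active 10% against placebo 2%: about 36%. Against 5%: about 15%.

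With a placebo rate of 3%, the 95% interval for the difference is about ±8.7 points at 6.56% and ±10.0 points at 10%. A comparison in one arm can estimate the difference but cannot be relied on to detect it.

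**The case against.** The strongest reply is that the comparison is already prespecified, twice, in 9.2.1 and 14.1.3. That is right. A reader might infer from 11.5.2.5 that thrombosis goes uncompared, and the text does not support that. What remains is that the promise does not reach the endpoint table or the named analysis, and the item has no components or time points.

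A reader might also infer that visits ask only about life-threatening thrombosis. They do not. Thromboembolic stroke is asked about without a limit, adverse events are scheduled for collection at every visit, everything reported is entered in the eCRF, and serious events are reported within 24 hours. Blood counts at screening and Visits 2 and 3 also support the haemoglobin and haematocrit criteria for the first week, though none is scheduled later. The fault is in what is labelled and counted as an endpoint, not in whether data exist.

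It is tempting to say that the commoner harm is the one left out, because 6.56% and 10% can be set against the 3–7% cited for symptomatic intracranial haemorrhage. The documents do not support that ranking. The rates come from patients treated for bleeding or urgent procedures. They are not broken down and may include strokes and deaths that are already endpoints. The 6.56% also lies inside 3–7%, and the bleeding endpoints cover much more than symptomatic intracranial haemorrhage. Nor does anything in the protocol measure what share of the benefit-risk question is affected.

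Finally, section 12.1.7 leaves the specification of key safety data to the Safety Management Plan and SAP, which were not available. Grouping of preferred terms may be settled there. Objectives, endpoint definitions and visit questions are protocol matters, however, and here the protocol's own statements conflict.

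**Conclusion.** The point holds as an internal inconsistency. Sections 9.2.1 and 14.1.3 commit to comparing all post-treatment thromboembolic and cardiovascular events. Sections 3.2 and 11.5.2.5 keep only recurrent ischaemic stroke. The visit review is narrower than 9.2.1 for other thromboembolism and narrower than 3.2 for extracranial bleeding. The consequence is undercounting in the endpoint review and no pooled thromboembolic comparison in the key safety analysis, although the events remain in the adverse event data.

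The size is about 3 to 5 active-group patients per arm with a thrombotic event of any kind. This assumes that the two cited rates carry over to stroke patients; the part not already counted as stroke or death cannot be worked out from the documents. Sample size and primary analysis are unaffected. This is a cheap improvement, worth making because the protocol itself names the risk.

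**What to change.** 1. Add to 3.2 (and synopsis 1.1.3.2) and to 11.5.2.5: incidence of any post-treatment thromboembolic or cardiovascular event, overall and by type, as referred to in 9.2.1 item 5. Use the time points already set for the other events (Days 7 and 90 for non-fatal events in 3.2; Days 7, 30 and 90 in 9.2.1).
2. Report it by arm as the difference in proportions with a 95% confidence interval, and state that the purpose is estimation.
3. In note w and in 6.5.2 to 6.5.6, reword the thromboembolic item to match 9.2.1 item 5, and the extracranial bleeding item to match the definition of major extracranial haemorrhage in 3.2.

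The cost is protocol wording, two eCRF labels and one table, with no new procedure and no change in sample size. The downside is one more safety comparison with few events and low power per arm.

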### 2.3.3 ASSESSMENT OF POTENTIAL RISKS AND BENEFITS

The STROACT is the first ever study to assess the efficacy and safety of sequential reperfusion therapy with the following scheme: non-vitamin K antagonist oral anticoagulant fast-acting specific reversal agent and intravenous thrombolysis therapy with rtPA.

There is an urgent clinical need to develop and assess the first causative (reperfusion) therapy for ischemic stroke patients on NOAC with anti-IIa/anti-Xa activity > 50 ng/ml or respective blood concentration of dabigatran. To minimize all peri-procedural risks and maximize patients' safety, we developed detailed and clear inclusion and exclusion criteria in accordance with EBM. The main safety endpoint is the rate of symptomatic intracranial haemorrhages (sICH). To follow-up these, in the management protocol we incorporated two neuroimaging testing (scanning) during the first week after randomisation: the first CT/MRI is going to be performed at 24 hours  $\pm$  4 hours after rtPA bolus, and MRI - 7 days  $\pm$  1 day (24 hours) from rtPA bolus.

All hospitals participating in the STROACT study are comprehensive stroke centres (CSC) with extensive experience in specific acute ischemic stroke treatments.

Incoming clinical safety data will be monitored and reviewed by IDMC to reassure patients' safety and scientific integrity of the study.

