#### 9.2.1.1 INTRACRANIAL HAEMORRHAGES

In the Safe Implementation of Thrombolysis in Stroke-Monitoring Study (SITS-MOST) symptomatic Intracranial Haemorrhage (sICH) is defined as the deterioration of stroke severity in NIHSS of  $\geq 4$  points with parenchymal haemorrhage type 2 (PH2) in neuroimaging (see [Section 9.1.3.3](#)).

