### 11.5.2.2 ANALYSIS OF THE SECONDARY ENDPOINT(S)

For each study arm (A, B or C) proportion of subjects randomized to placebo and active treatment and proportion difference together with 95% CI will be presented. Unadjusted and adjusted (with subject age) odds ratios will be shown. P value lower than 0.05 will be considered as statistically significant ( $\alpha=0.05$ ).

---

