#### 11.5.2.6 ADVERSE EVENTS ANALYSIS

Any undesirable signs, symptoms or medical conditions occurring or worsening of pre-existing conditions between signing informed consent and the first administration study medication are considered as pre-treatment AEs. Undesirable signs, symptoms or medical conditions or worsening of pre-existing conditions occurring after the first administration of study medication are considered as treatment emergent adverse events (TEAEs).

A TEAE will be analysed as related to study medication (i.e. as adverse drug reaction, ADR) if the relationship to study treatment was documented as “unlikely”, “possible”, “probable”, or “definite” or if the relationship to study treatment is missing.

An overview table presenting the incidence of the following AE categories will be presented. Percentage of patients in each category will be compared between treatments as a difference in proportions between treatments including a 95% CI based on the (Agresti and Caffo, 2000).

All AEs

- Pre-treatment AEs
- Serious AEs (SAEs) (including pre-treatment SAEs)
- Treatment emergent SAEs (TESAEs)
- Severe TEAEs
- Related TEAEs
- Related severe TEAEs
- TEAEs leading to permanent discontinuation (i.e. withdrawal) of study medication
- Related TEAEs leading to permanent discontinuation of study medication
- AEs leading to death (i.e., outcome of AE is fatal)
- TEAEs leading to death
- Related TEAEs leading to death

All treatment emergent AEs (TEAEs) and all serious TEAEs will be tabulated by MedDRA SOC and PT presenting the number and percentage of patients reporting the AE and the number of AEs reported. Additional tables will distinguish the events by whether the AE was related to study medication and by maximum severity.

All AEs documented in the eCRF will be listed by patient. Data listings will include patient ID, treatment group, verbatim term, preferred term, system organ class, start and stop date and relative day of the AE, severity, medications (yes/no), seriousness, action taken with study medication, relationship to study medication, and outcome will be provided. TEAEs will be flagged as such. In addition, separate listings for all SAE's, deaths and AEs leading to discontinuation (action taken with study treatment = drug withdrawal or AE is reason for early termination) will be presented.

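### Per-arm odds ratios, above all the age-adjusted one, are a poor choice for sICH: with about 1.4–3.5 events expected on active treatment, at least one arm is likely to give no usable estimate

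*Protocol*

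**What the plan says.** Section 2.3.3 ranks the safety outcomes: "The main safety endpoint is the rate of symptomatic intracranial haemorrhages (sICH"). Section 9.2.1.1 defines sICH as NIHSS worsening of at least 4 points "with parenchymal haemorrhage type 2 (PH2) in neuroimaging".

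Section 11.5.2.5 covers symptomatic and asymptomatic intracranial haemorrhage, major extracranial haemorrhage, death, recurrent ischaemic stroke and neurological deterioration in one sentence, and says that they "will be analysed in the same way as secondary endpoints".

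Section 11.5.2.2 gives that method. The unit is the single NOAC arm ("For each study arm (A, B or C")). For each arm the "proportion difference together with 95% CI will be presented", and in addition "Unadjusted and adjusted (with subject age) odds ratios will be shown", with significance at p<0.05. The interval for the difference is not named.

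Section 11.5.2.6 names one for the adverse-event overview table: a "95% CI based on the (Agresti and Caffo, 2000").

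On frequency, section 2.3.1 says of sICH after rtPA that it is a complication "which occurs in 3-7% of all treated patients". No sICH rate is given for placebo.

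**The concern.** An odds ratio from a two-by-two table is zero, infinite or undefined as soon as one treatment group has no events, and a maximum-likelihood logistic model then has no finite treatment coefficient. Adding age as a covariate does not help. Even when both groups have an event, a model with treatment and age fitted to a handful of events gives an estimate of little value.

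The protocol leaves much to the analysis plan, but here it fixes the model, the unit of analysis and the threshold itself. It applies to a rare event a method that section 11.5.2.2 sets out for the secondary endpoints. The ordinary adverse-event table, meanwhile, has a named small-sample interval that the main safety endpoint lacks.

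At stake is how the sICH results can be reported: odds ratios that software prints as huge numbers or not at all, and a risk-difference interval that could exclude zero or not depending on an unstated choice.

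**Working it through.** **1. The plan's own group size.** Section 11.3 gives 40% response in both groups, a 15% margin, one-sided alpha 0.20, power 70%, one interim and 10% drop-out.

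- Fixed design: n = (0.8416 + 0.5244)² × 2 × 0.4 × 0.6 / 0.15² = 39.8 per group.
- One interim at half information with Hwang-Shih-DeCani spending: gamma = −4 is an assumption, supported because it reproduces the interim alpha of 0.0238 in 11.5.4.1. It inflates n by 1.006 to 40.05, so 41.
- Drop-out: 41 / 0.9 = 45.6, so 46.

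The stated 46 per group (92 per arm) is reproduced. Section 1.1.9 plans about 100 per arm, that is 50 per group.

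**2. Expected sICH events on active treatment, per arm.** 46 × 0.03 = 1.4 to 46 × 0.07 = 3.2. With 50 per group: 1.5 to 3.5.

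**3. Chance of no finite odds ratio in one arm.** P = 1 − [1 − (1 − pA)ⁿ] × [1 − (1 − pP)ⁿ], where pA is the active rate (protocol, 3–7%) and pP the placebo rate (assumed). Example at n = 46, pA = 5%, pP = 1%: 0.95⁴⁶ = 0.094 and 0.99⁴⁶ = 0.630, so P = 1 − 0.906 × 0.370 = 0.665.

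| Assumed placebo rate | n = 46; active 3 / 5 / 7% | n = 50; active 3 / 5 / 7% |
|---|---|---|
| 0.5% | 85 / 81 / 80% | 83 / 80 / 78% |
| 1% | 72 / 67 / 64% | 69 / 64 / 62% |
| 2% | 54 / 45 / 42% | 50 / 41 / 38% |
| 3% | 43 / 32 / 27% | 39 / 28 / 24% |

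The chance passes one half only if the placebo rate is below about 2.3 / 1.7 / 1.6% (n = 46) or 2.0 / 1.6 / 1.4% (n = 50), for active 3 / 5 / 7%.

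**4. At least one of three arms affected.** 1 − (1 − P)³, with the same rates in each arm and n = 46: 62% at 7% v 3%, 82% at 3% v 3%, 96% at 5% v 1%.

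**5. When the odds ratio is finite.** Total sICH expected per arm at n = 46: 46 × (0.05 + 0.01) = 2.8, or 46 × (0.07 + 0.03) = 4.6. The chance of fewer than 10 events in an arm is at least 98% at these rates. An age-adjusted model would rest on that.

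**6. The difference in proportions.** It exists with zero cells, but the interval matters (n = 46):

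- 4 v 0, Wald: 0.0870 ± 1.96 × √(0.0870 × 0.9130 / 46) = +0.6% to +16.8%, excluding zero.
- 4 v 0, Agresti-Caffo (one event and one non-event added per group, so 5/48 v 1/48): −1.2% to +17.9%, including zero.
- 0 v 0: Wald has zero width; Agresti-Caffo is ±5.7%.
- Exact coverage of the nominal 95% interval, summing binomial probabilities over all tables, for active 3–7% and placebo 0.5–2%: Wald 75–95%, Agresti-Caffo 96–100%.

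**7. Power per arm.** Two-sided Fisher at 46 v 46: 4 v 0 gives p = 0.117, 5 v 0 gives 0.056, 6 v 0 gives 0.026. At least six events against none are needed for p<0.05.

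**The case against.** **The plan does deliver a result for sICH.** A reader might infer that the main safety endpoint has no workable analysis. The documents do not support that: 11.5.2.2 requires both proportions and their difference with a 95% interval, and the odds ratios are shown in addition. This objection stands, and the point is confined to the odds ratios and to the choice of interval.

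**The odds ratio need not usually fail.** A reader might also infer that it fails in most arms. That rests on a placebo rate the protocol does not give. At 2% placebo with 5–7% active, or at 3% placebo with any active rate in the range, the zero-cell chance in an arm is below one half. Placebo patients are enrolled with anticoagulant activity above 50 ng/mL or, on dabigatran, on reported recent intake, so a near-zero rate cannot be presumed. This stands too.

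**sICH is not every key safety endpoint.** The 3–7% is for sICH only. The protocol gives no rate for death or major bleeding, and at an illustrative 10% in both groups the zero-cell chance at n = 46 is 1.6%. Fatal adverse events already receive an Agresti-Caffo interval in 11.5.2.6. The point therefore covers sICH and whichever other key endpoints turn out to be rare.

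**Interval type and pooled tables belong in the SAP.** Agreed: an unnamed interval or the absence of a pooled table would not be a finding alone. But the protocol does not leave the odds-ratio model open. It states the model, per arm, for these endpoints, and that stated choice suits rare events badly.

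**Per-arm reporting is deliberate.** Section 2.3.2 says the potential harms of andexanet alfa differ from those of idarucizumab. The lack of a pooled comparison is therefore not an error.

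**Conclusion.** The point holds in a limited form. The protocol fixes per-arm crude and age-adjusted odds ratios for its main safety endpoint. With 1.4–3.5 active events expected per arm, these are likely to be non-estimable or uninformative in at least one arm: 62–96% for no finite odds ratio in at least one of three arms in the scenarios shown. For a single arm the chance is 62–85%, 38–54% or 24–43% at a placebo rate of 0.5–1%, 2% or 3%.

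This rests on the protocol's 3–7% carrying over to the sequential treatment, on the assumed placebo rates, and, for the three-arm figure, on equal rates across arms. The difference in proportions survives, but a Wald version of its interval would be unreliable at these counts, and the protocol already cites a better one elsewhere. The defect is worth correcting before analysis; it does not leave sICH unanalysed.

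**What to change.** In section 11.5.2.5, replace the bare reference to the secondary-endpoint method as follows:

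- For sICH and any other key safety endpoint with few events, make the per-arm risk difference with the Agresti-Caffo 95% interval, as in 11.5.2.6, the main summary.
- For these endpoints, replace the age-adjusted maximum-likelihood odds ratio by a Firth-penalised one, or omit it. State the event count below which this applies.
- Optionally, add a risk difference pooled over the three arms and stratified by NOAC as supportive, keeping the per-arm results beside it because the antidotes differ.
- State that a non-significant per-arm result is not evidence of safety. The changes above do not add power.

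The cost is wording in the protocol or SAP, slightly wider intervals and a few extra table lines. Trial conduct and sample size do not change.
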